#### Faecal calprotectin

FCAL will be measured at baseline and 12 weeks. FCAL is a sensitive marker of intestinal inflammation and has been shown to correlate to histological and endoscopic inflammation and disease activity measures.^(54,55)^

Faecal samples for FCAL will be collected in an ELISA kit (Epitope Diagnostic) and stored at −80 °C until all samples are collected. FCAL will be determined with a range of 0–321 μg/g or 0–892 ng/ml calprotectin. The analytical sensitivity (LLOD) of the human calprotectin ELISA as determined by the 95 % confidence limit on 12 duplicate determination of zero standard is approximately 2⋅5 ng/ml. A LLOQ was determined by dilution of assay standards and it is approximately 5 ng/ml.

#### Gastrointestinal symptoms

Gastrointestinal symptoms will be assessed via the IBD Symptom Inventory-Short Form (IBDSI-SF)^(56)^ and stool consistency self-rated against Bristol Stool chart. These outcomes will be assessed at baseline, 6 weeks, and 12 weeks, to detect any beneficial or adverse changes due to the intervention.

Cognition, memory and mood will be assessed at baseline and 12 weeks via the Stroop test, Rey Auditory Verbal Learning Task (RAVLT) and DASS-21 questionnaire.

#### Data collection procedures

Two weeks prior to study commencement, participants will receive faecal sample testing kits by mail with instructions for collection one day prior to their baseline online appointment. Participants will attend a baseline online meeting for completion of a demographic and health surveys, completion of the cognitive performance, mood and attention tests, and instructions regarding ongoing study assessments. Participants will return completed faecal samples by express post and will receive intervention products. Participants will be instructed to avoid making dietary changes throughout the intervention period and refrain from introducing new dietary products or supplements containing probiotics or prebiotics. Brief education on these products will be provided by an Accredited Practising Dietitian. Dietary intake will be captured by three 24 h dietary recalls completed on non-consecutive days at baseline, 6 and 12 weeks. Participants will be required to recall all food and drink items consumed in the previous 24 h period on two weekdays and one weekend day. This will be completed using the online Intake24 multiple-pass dietary recall system,^(57–59)^ in which all foods and drinks are coded to the AUSNUT 2011–13 database.^(60)^ Dietary recalls will be collected using REDCap electronic data collection tools,^(61,62)^ with summaries of intake then imported by the researchers into FoodWorks Professional nutrient analysis software.^(63)^ Dietary intake will also be analysed for dietary polyphenol content using Phenol-Explorer database.^(64)^ Participants will be instructed to remain on required medical therapy throughout the intervention. Demographic and health surveys will be delivered online to participants via REDCap.

To improve participant adherence, the participants will receive email and SMS contact in advance of every visit and mid-way assessments. Telephone contact will be made if no replies through email or SMS are received. If participants fail to attend treatment sessions, researchers will enquire as to the reasons for non-attendance and aim to encourage adherence to treatment and attendance at sessions via telephone contact. Participants will be provided with a checklist and requested to complete it each day indicating whether they consumed the study products. As an additional marker of compliance, participants will be required to inform the researchers of any remaining products at the end of the intervention. Participants will also be asked a question in the dietary assessment Intake 24 instrument about their consumption of the provided supplements on the previous day. Affirmative responses will be summed across the 3 days for each of the time points at which the dietary assessment is conducted (for example, if participants report taking the supplements on only one of the 3 days this will indicate 33 % compliance).

### Statistical analysis

Statistical analyses will be performed in Stata software,^(65)^ R software^(66)^ and/or IBM SPSS Statistics.^(67)^ An ITT analysis will be the primary analysis, including all participants randomised and analysed according to the treatment group to which they were originally assigned. A per-protocol analysis will additionally be conducted for all outcomes and used as a sensitivity analysis compared to the ITT. The per-protocol analysis will include participants who completed the trial without major violation including medical disruptions or unblinding, and who exhibited >80 % compliance to the intervention products.

Baseline demographics and measurements will be reported for each intervention group as means and standard deviations or 95 % CI.

The primary outcome will be the mean IBDQ-32 score at week 12 adjusted for baseline and covariates and assessed using an ANCOVA. A sensitivity analysis of differences in within-group change in IBDQ-32 score from baseline to week 12 will be measured using a two-sample *t*-test or Mann–Whitney *U*-test depending on normality of distribution. Within-group differences in secondary outcomes measured at two timepoints will be evaluated using a two-sample *t*-test or Mann–Whitney *U*-test depending on normality of distribution. Within-group differences in secondary outcomes measured at three time points will be evaluated using linear mixed modelling. Between-group differences of outcomes will be explored using ANOVA or ANCOVA if covariates need to be considered or mixed models. Relevant covariates associated with the primary outcome of health-related quality-of- life will be included in the analyses. Secondary analyses will be conducted to investigate relationships between changes in outcome measures. Predictors and assumptions of missing data will be investigated. Methods such as multiple imputation will be considered depending on the data missing. Appropriate sensitivity analyses will be performed.

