#### Sample size and power calculations

Our sample size (*n* 100) was calculated in G*Power Version 3.1.9.6 based on the primary outcome measure of a clinically relevant change in mean score of ≥16 in the 32-item Inflammatory Bowel Disease Questionnaire (IBDQ-32).^(39,40)^ The primary comparison of interest is between the combined intervention versus control. Assuming a mean change in the IBDQ-32 score of 16 ± 20 estimated from previous literature,^(41–44)^ α- significance of 0⋅05 and power 95 %, a sample size of n 19 per arm is required with effect size of 0⋅8. To allow for ~25 % drop-out, given the duration of this trial and based on previous literature,^(45–47)^
*n* 25 participants will be recruited to each arm.

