#### Health-related quality of life (HRQOL)

The primary outcome of HRQOL will be measured using the IBDQ-32. The IBDQ-32 is a validated 32-item self-reported questionnaire, assessing quality of life (QOL) across four disease-specific sub-categories: bowel symptoms (ten questions); systemic symptoms including sleep disorders and fatigue (five questions); emotional function (twelve questions); and social function (five questions).^(49)^ The total score ranges from 32 to 224 points, with lower scores reflecting lower HRQOL. Each question is scored using a 7-point Likert scale ranging from 1 (low QOL) to 7 (high QOL). All participants will complete the IBDQ-32 at baseline, 6 weeks, and 12 weeks. The change in total IBDQ-32 score has been demonstrated to detect, with reliability and sensitivity, changes in disease activity and endoscopic mucosal healing in response to treatment.^(40,50,51)^ A change in total score of ≥16 points has been shown to correlate to a clinically meaningful change in QOL.^(39,40)^

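### The primary week-12 ANCOVA comes with no committed missing-data method and leaves out the week-6 IBDQ-32, so it may fall short of the promised all-randomised analysis

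*Protocol article*

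**What the plan says.** All references are to the protocol article.

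- **Population (Statistical analysis):** "An ITT analysis will be the primary analysis, including all participants randomised and analysed according to the treatment group to which they were originally assigned".
- **Primary model (same section):** "The primary outcome will be the mean IBDQ-32 score at week 12 adjusted for baseline and covariates and assessed using an ANCOVA".
- **Missing data (same section):** predictors and assumptions will be looked into, imputation may be used depending on what is missing, and sensitivity analyses will be done. No primary method is fixed.
- **Other models (same section):** linear mixed modelling is assigned to within-group differences in secondary outcomes with three time points. Mixed models also appear in a list of options for exploring between-group differences.
- **Measurement schedule (Health-related quality of life):** "All participants will complete the IBDQ-32 at baseline, 6 weeks, and 12 weeks". Table 1 adds the IBDQ-32 at an early termination interview.
- **Expected loss (Sample size and power calculations):** "To allow for ~25 % drop-out, given the duration of this trial and based on previous literature", the 19 required per arm become 25 recruited.
- **Follow-up of leavers (Inclusion and exclusion criteria):** participants who change medication, do not comply or leave are to be encouraged to keep giving outcome data and attend the final visit, so that they can enter the intention-to-treat analysis.

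**The concern.** The population and the model do not meet unless something is done about missing week-12 scores, and the protocol does not say what. An ANCOVA of a single visit uses only people with a score at that visit. A trial that budgets for losing a quarter of its participants should know in advance how the primary estimate handles them. Otherwise the choice is made after the pattern of missing data is seen.

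The IBDQ-32 is a measure of how participants feel, so poor scores at week 6 could plausibly predict who has no score at week 12. If so, the people with week-12 scores are a selected group, and the difference between the combination and double placebo may be distorted. The week-6 score carries information on that selection and is already being collected, but the named primary model does not use it.

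**Working it through.** **1. The plan's own figures.** The sample-size section requires 19 per arm, allows about 25% drop-out and recruits 25.
- 19 / (1 − 0.25) = 25.3, which rounds up to 26; the plan states 25.
- 25 × 0.75 = 18.75, or about 19.

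So the plan expects about 19 evaluable participants of 25 per arm. (The 19 itself does not reproduce for a two-arm t-test at 95% power, which needs 42 per arm two-sided. That is a separate matter and is not used here.)

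**2. Who an observed-data ANCOVA would include**, if the whole allowance becomes missing week-12 scores:
- whole trial: 100 × 0.75 = 75 analysed, 25 omitted;
- combination and double placebo: 50 × 0.75 = 37.5, so 37 or 38 analysed.

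This is an upper figure, because leavers may still attend the final visit.

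**3. Size of any bias.** The documents give the difference of 16, the SD of 20 ("Assuming a mean change in the IBDQ-32 score of 16 ± 20 estimated from previous literature") and 25 per arm. Everything else below is assumed. In both simulations all drop-out comes after week 6. The week-6 analysis is a likelihood analysis that regresses week 6 on arm and baseline in everyone, and week 12 on arm, baseline and week 6 in those observed. Under this drop-out pattern it gives the point estimate of a repeated-measures model with unstructured covariance.

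*Simulation A* (4,000 trials per row): score SD 20, correlation of baseline with each later visit 0.5, week-6 effect 8. The SD of change is 20 × √(2 × (1 − 0.5)) = 20, which agrees with the plan.

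| Drop-out mechanism | Week 6–12 correlation | ANCOVA, observed data: mean (SD) | Using week 6: mean (SD) |
|---|---|---|---|
| Completely random, 25% | 0.5 | 15.99 (5.76) | 15.98 (5.70) |
| | 0.7 | 15.99 (5.80) | 15.97 (5.49) |
| | 0.85 | 15.95 (5.75) | 15.96 (5.23) |
| Low week-6 score leaves, both arms, 23% | 0.5 | 15.48 (5.74) | 15.72 (5.74) |
| | 0.7 | 15.58 (5.65) | 16.03 (5.45) |
| | 0.85 | 15.44 (5.58) | 16.02 (5.25) |
| Opposite directions by arm, 26% (extreme) | 0.5 | 13.80 (5.83) | 16.10 (5.94) |
| | 0.7 | 11.85 (5.72) | 15.95 (5.60) |
| | 0.85 | 10.52 (5.65) | 15.99 (5.35) |

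- *Random drop-out:* no bias by either method. The standard error falls by 1 − 5.70/5.76 = 1%, 1 − 5.49/5.80 = 5% and 1 − 5.23/5.75 = 9%.
- *Same direction in both arms:* ANCOVA falls short of 16 by 0.52, 0.42 and 0.56. Simulation error is about 5.74/√4000 = 0.09. The week-6 analysis is unbiased under this mechanism, so its 15.72 in the first row is simulation error that the ANCOVA shares. The gap between methods is the cleaner measure: 0.24, 0.45 and 0.58.
- *Opposite directions:* ANCOVA falls short by 2.2 to 5.5 points, while the week-6 analysis stays within 0.1 of 16.

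*Simulation B* (1,500 trials): score SD 25; correlations 0.6 (baseline to week 6), 0.5 (baseline to week 12) and 0.75 (week 6 to week 12); week-6 effect 10. Drop-out depends on the week-6 score: 32% control, 23% active, 28% overall. Observed-data ANCOVA averages 14.93 (SD 7.09), the week-6 analysis 16.03 (SD 6.94), and full data 16.06 (SD 6.12). The ANCOVA shortfall is 16 − 14.93 = 1.07 points, or 1.07/7.09 = 0.15 of the estimator's SD. Here the SD of change is 25 × √(2 × 0.5) = 25, above the plan's 20.

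**The case against.** The strongest reply is that nothing here is broken. A baseline-adjusted ANCOVA at the endpoint is a standard primary analysis. After multiple imputation it can include all 100 participants and use week 6 in the imputation model. The protocol names imputation, promises sensitivity analyses and encourages leavers to attend the final visit. Details of imputation commonly sit in a statistical analysis plan, which is not shown.

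Much of this stands, and it rules out several stronger readings:

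- *That the ANCOVA cannot include everyone randomised.* With imputation it can.
- *That the plan specifies a completers-only analysis.* It never says so. That result follows only if nothing is imputed.
- *That 25 participants will be lost from the analysis.* The 25% is a planning allowance, and stopping treatment need not mean a missing score.
- *That loss will be heavier on placebo, so the estimate is biased.* The documents do not support this. The Probiotic intervention section lists gastrointestinal side effects, so loss could be heavier on active product.
- *That mixed models are barred for the primary outcome.* The three-time-point sentence concerns within-group differences in secondary outcomes, and the list of between-group options is not limited to secondary outcomes.

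What does not stand is that this is only missing detail. The protocol itself states an all-randomised population, a primary model limited to week 12 and imputation that is conditional on the data. An analysis plan that followed this text would inherit the mismatch.

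**Conclusion.** The point holds as a cheap improvement. The primary model as named does not by itself deliver an analysis "including all participants randomised and analysed according to the treatment group to which they were originally assigned", no committed method closes the gap, and week-6 scores are not part of that model.

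The likely numerical effect is modest. Bias is roughly 0.5 to 1 point on 16 when drop-out follows the week-6 score in moderate settings, and smaller if week 6 predicts week 12 only weakly. It reaches several points only when drop-out differs strongly by arm. There is none if drop-out is completely random, where the gain is a 1% to 9% smaller standard error. These sizes rest on assumed correlations, drop-out mechanisms and week-6 effects, and on all drop-out occurring after week 6. Week 6 cannot help for people who leave before giving that score. The simulations do not show that this trial's estimate will be biased.

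**What to change.** Commit to one primary method that uses week 6, before the analysis begins. Either:

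1. a repeated-measures mixed model of the IBDQ-32 at weeks 6 and 12 (REML, unstructured covariance) with arm, visit, arm-by-visit, baseline and baseline-by-visit, reporting the week-12 contrast of combination minus double placebo with its 95% CI; or
2. the week-12 ANCOVA after multiple imputation by arm, with baseline, week-6 and early-termination scores in the imputation model, reporting the same contrast and interval.

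Under either option:
- State that early-termination scores are not counted as week 12. A two-visit model has no natural place for them; an imputation model does.
- State how participants with no post-baseline score are included, for example by imputation. The mixed model alone would omit them.
- Keep the observed-data week-12 ANCOVA as a sensitivity analysis.
- Add one delta-adjusted analysis for drop-out that is not at random.

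The cost is a change of wording and slightly more analysis work, with no new data. The downside is that the primary result then relies on a missing-at-random assumption, which the delta-adjusted analysis is there to test.

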#### Secondary outcome measures

Shotgun metagenomic sequencing of faecal microbiota samples will be performed at baseline and 12 weeks, to profile the taxonomic composition and functional potential of all microbial communities present in the faecal microbiota.^(52)^ This sequencing will capture any changes to the composition and functional potential of the faecal microbiota after the intervention.

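### Baseline-to-week-12 changes within an arm are assigned independent-samples tests, which ignore the pairing; the error is conservative and limited to secondary within-arm results

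*Protocol article*

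**What the plan says.** All the analysis rules are in the Statistical analysis section of the protocol article. For secondary outcomes with two measurements: "Within-group differences in secondary outcomes measured at two timepoints will be evaluated using a two-sample" t-test or "Mann–Whitney *U*-test depending on normality of distribution". For those with three: "Within-group differences in secondary outcomes measured at three time points will be evaluated using linear mixed modelling". Comparisons between arms have a separate rule: "Between-group differences of outcomes will be explored using ANOVA or ANCOVA if covariates need to be considered or mixed models". No paired t-test or Wilcoxon signed-rank test is named anywhere.

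The outcome sections show which variables fall under the two-timepoint rule. "FCAL will be measured at baseline and 12 weeks"; "Shotgun metagenomic sequencing of faecal microbiota samples will be performed at baseline and 12 weeks"; "Cognition, memory and mood will be assessed at baseline and 12 weeks". Table 1 gives SCCAI the same two scheduled interviews, plus the early-termination interview. The Bristol Stool Chart is unclear: Table 1 marks two timepoints, while the Gastrointestinal symptoms section lists three.

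**The concern.** FCAL at entry and FCAL at week 12 in one arm are two readings from the same people. A two-sample t-test or Mann–Whitney U-test treats them as readings from two unrelated sets of people. It therefore leaves out the covariance that normally makes a before/after difference more precise than either reading alone.

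This is not a detail left to a later document. The article names a method, and the method does not fit the contrast it is assigned to. If it is followed, the within-arm p-values and intervals for FCAL and the other two-timepoint outcomes will be wrong. If the analyst switches to a paired test after seeing the data, that will be an unplanned departure from the published plan.

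**Working it through.** **Inputs.** The named tests and measurement times are as set out above. The Sample size section gives 19 evaluable participants per arm, 25 recruited, a standardised effect of 0.8 and a significance level of 0.05. The article gives no figure for the within-arm tests, so there is none to reproduce. Here 19 and 25 serve only as arm sizes, and 0.8 only as an illustrative effect: it was set for IBDQ-32, not for FCAL or any outcome under this rule. Whether 19 per arm is right for the between-arm comparison is a separate question. The baseline-to-week-12 correlation r is not in the document and is assumed over a range. Equal variances, normal data and two-sided tests are also assumed.

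**Step 1: standard error.** With outcome SD σ and n people measured twice:

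- true variance of the mean change = 2σ²(1 − r)/n
- variance used by the two-sample test = 2σ²/n
- ratio of standard errors = 1/√(1 − r)

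This gives 1/√0.7 = 1.20, 1/√0.5 = 1.41 and 1/√0.3 = 1.83.

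**Step 2: type I error.** In large samples, the two-sample test at nominal 0.05 rejects only when the correctly scaled statistic exceeds 1.96/√(1 − r). At r = 0.5 that is 2.77, a two-sided error of 0.0056; at r = 0.7 it is 3.58, an error of 0.0003. Simulation at the trial's arm sizes (40,000 replicates, bivariate normal) agrees closely. The paired test stays between 0.049 and 0.051 throughout.

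| r (assumed) | SE ratio | Type I error, n = 19 | Type I error, n = 25 |
|---|---|---|---|
| 0 | 1.00 | 0.050 | 0.051 |
| 0.3 | 1.20 | 0.021 | 0.019 |
| 0.5 | 1.41 | 0.008 | 0.007 |
| 0.7 | 1.83 | 0.001 | 0.0006 |

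The Mann–Whitney test behaves the same way: 0.019, 0.007 and 0.0006 at n = 25 for r = 0.3, 0.5 and 0.7 (5,000 replicates).

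**Step 3: power at n = 19.** The size of the loss depends on the unit in which the effect is fixed, so both are shown.

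| r (assumed) | 0.8 SD of the change: paired | two-sample | 0.5 SD of the outcome: paired | two-sample |
|---|---|---|---|---|
| 0.3 | 0.91 | 0.85 | 0.42 | 0.30 |
| 0.5 | 0.91 | 0.73 | 0.54 | 0.27 |
| 0.7 | 0.91 | 0.44 | 0.76 | 0.23 |

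In the first pair of columns the raw effect shrinks as r rises, because the SD of the change is σ√(2(1 − r)). At r = 0.7, 0.8 SD of the change is only 0.62 SD of the outcome.

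**The case against.** **It may be a wording slip.** The sentence just before uses the same test names for differences in within-group change in IBDQ-32. That can be read as comparing change scores between two arms, where a two-sample test is valid, so the secondary-outcome sentence may be a shortened copy. This cannot be excluded, and the IBDQ-32 sentence is not criticised here. But between-group contrasts have their own rule, and the fallback is Mann–Whitney rather than signed-rank, so the text as it stands does not describe a paired test. Either way the sentence needs correcting.

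**The consequences are limited.** This stands. The primary analysis is a baseline-adjusted ANCOVA of week-12 IBDQ-32. The Sample size section says: "The primary comparison of interest is between the combined intervention versus control". That is a between-arm contrast and is unaffected.

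**Stronger readings that the document does not support.**

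- A reader might infer that the hypotheses on FCAL all rest on the faulty test. Hypothesis 2 (the combination against each intervention alone) is a between-arm question under the ANOVA/ANCOVA/mixed-model rule. Hypothesis 3 (FCAL change explained by microbiome change) belongs to the planned analyses of relationships between changes. Only hypothesis 1 could plausibly be answered by the within-group rule, and in a placebo-controlled trial it too is naturally between-arm.
- A reader might infer that the ANOVA option is an equal error, costing 25% to 49% of residual variance. The article already allows ANCOVA and says relevant covariates will be included. That range holds only against ANOVA of raw week-12 values (r² = 0.25 at r = 0.5, 0.49 at r = 0.7). Against ANOVA of change scores, the variance goes from 2(1 − r) to 1 − r²: 1.00 to 0.75 at r = 0.5 (25%), but 0.60 to 0.51 at r = 0.7 (15%). The text does not say which would be used.
- A log scale for FCAL cannot be called for from the article, which gives no FCAL distribution.

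**Conclusion.** The rule is wrong as written: independent-samples tests are assigned to a paired contrast. For any positive within-person correlation the standard error is too large by 1/√(1 − r), p-values are too large and power is lost. Over the assumed range 0.3 to 0.7 the inflation runs from 1.20 to 1.83. The loss is modest at r = 0.3 and serious at r = 0.7; at r = 0 the two kinds of test nearly agree. The exact figures rest on assumed correlations, equal variances and normality. The direction needs only positive correlation, which is what repeat readings on the same patient normally show.

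The error is conservative. It can hide real within-arm changes, but it does not inflate false-positive claims. It is confined to secondary within-arm inference, so it is a correction of moderate weight and not a threat to the trial's main conclusion.

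**What to change.** In the Statistical analysis section, replace the tests named for two-timepoint secondary outcomes with a paired t-test or, where the within-person differences are clearly non-normal, a Wilcoxon signed-rank test. State that normality is judged on the differences. If a between-arm comparison of change scores was intended, say so instead.

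Add a sentence that within-arm changes are supportive and that conclusions about treatment effect come from the between-arm comparison. That comparison is preferably an ANCOVA of the week-12 value adjusted for the same outcome's baseline, as already planned for IBDQ-32. Separate within-arm tests cannot show that one arm did better than another.

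Reconcile the Bristol Stool Chart schedule between Table 1 and the Gastrointestinal symptoms section, so that it is clear which rule applies to it.

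The cost is a few sentences of wording, to be settled before unblinding. No new data, visits or participants are needed.

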### Research aim and objectives

This study aims to evaluate the combined effect and clinical significance of a multi-strain probiotic intervention (VSL#3®^,^ containing one strain of *Streptococcus thermophilus*, three strains of *Bifidobacterium* and four strains of *Lactobacillus*) provided together with dietary anthocyanins extracted from New Zealand-grown blackcurrants on the gut microbiota profile and inflammatory biomarkers in adults with UC.

We hypothesise that (1) anthocyanins, in combination with probiotics, will result in a reduction in gut inflammation measured by faecal calprotectin (FCAL) and will modulate the gut microbiome measured through shotgun metagenomic sequencing of faecal samples; (2) anthocyanins, in combination with probiotics, will result in a synergistic effect that results in a significantly greater reduction in FCAL and improvement in the gut microbiome than each intervention alone; (3) the reduction in FCAL will be explained by beneficial changes to the gut microbiome profile; and (4) these changes in FCAL and the gut microbiome will lead to clinically significant improvements in health-related quality-of-life measured with the IBDQ-32.

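### Baseline adjustment of the secondary between-group comparisons is optional with no stated criterion, and the covariate rule does not name each outcome's own baseline value

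*Protocol article*

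**What the plan says.** All analysis statements are in the Statistical analysis section of the protocol article.

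- Primary outcome: "The primary outcome will be the mean IBDQ-32 score at week 12 adjusted for baseline and covariates and assessed using an ANCOVA". Baseline adjustment is unconditional here.
- Between-group comparisons in general: "Between-group differences of outcomes will be explored using ANOVA or ANCOVA if covariates need to be considered or mixed models". The article does not say when covariates would need considering, or whether an ANOVA would use week-12 values or change.
- Covariate rule: "Relevant covariates associated with the primary outcome of health-related quality-of- life will be included in the analyses".
- Outcomes with two timepoints: "Within-group differences in secondary outcomes measured at two timepoints will be evaluated using a two-sample" t-test or Mann–Whitney test. That sentence concerns within-group differences, so it adds nothing on adjustment between arms.

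The baseline values exist. "FCAL will be measured at baseline and 12 weeks"; "Shotgun metagenomic sequencing of faecal microbiota samples will be performed at baseline and 12 weeks"; "Cognition, memory and mood will be assessed at baseline and 12 weeks". Table 1 also shows SCCAI at the first and second interviews.

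The second hypothesis, under Research aim and objectives, is that the combination "results in a significantly greater reduction in FCAL and improvement in the gut microbiome than each intervention alone". That is a claim about differences between arms.

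**The concern.** The article treats the primary and secondary outcomes differently without giving a reason. For IBDQ-32 the baseline score is always in the model. For FCAL and the other two-timepoint outcomes it enters only if someone judges covariates necessary.

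The covariate rule does not close the gap. It is tied to IBDQ-32, and a variable associated with quality of life need not be the baseline value of FCAL or RAVLT. The primary-outcome sentence also lists baseline separately from covariates, so the article's own usage does not make an outcome's baseline one of its covariates.

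Two things are at stake. The first is precision, in arms of 25 that are planned to fall to about 19 after drop-out. The second is pre-specification: a conditional rule with no criterion lets the model be chosen after baseline imbalance, or the result, has been seen.

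**Working it through.** **The plan's own figure.** The article gives no power or effect size for FCAL or any other secondary outcome, so there is no stated figure to reproduce. The only sizing is for IBDQ-32 (16 ± 20, standardised difference 0.8, 19 per arm, 95% power). A two-sided two-sample t-test at 0.05 with those inputs has 67.0% power at 19 per arm. That mismatch is a separate matter and is not relied on here.

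**Inputs.** From Sample size and power calculations: n = 19 per arm after drop-out, 25 recruited. Assumed: standardised difference d = 0.8 on the week-12 value (borrowed from IBDQ-32), with d = 0.5 as an alternative; two-sided 0.05; correlation ρ between baseline and week 12 of 0.3, 0.5 and 0.7; equal SD σ at both times.

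**Variances for a comparison of two arms.**

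- ANOVA of week-12 values: σ²
- ANOVA of change: 2σ²(1 − ρ)
- ANCOVA: σ²(1 − ρ²)

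The ratio of ANCOVA to week-12 ANOVA is 1 − ρ², giving 0.91, 0.75 and 0.51. The ratio of ANCOVA to change-score ANOVA is (1 − ρ²) / [2(1 − ρ)] = (1 + ρ)/2, giving 0.65, 0.75 and 0.85. Neither ratio can exceed 1.

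**Power.** Noncentral t with noncentrality d* × √(n/2), where d* is d, d/√(2(1 − ρ)) or d/√(1 − ρ²). Degrees of freedom are 2n − 2, or 2n − 3 for ANCOVA. Example at n = 19, d = 0.8, ρ = 0.5: √9.5 = 3.082. Unadjusted noncentrality is 0.8 × 3.082 = 2.47. For ANCOVA, 0.8/0.866 = 0.924, and 0.924 × 3.082 = 2.85.

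| n per arm | d | ρ | Week-12 ANOVA | Change ANOVA | ANCOVA |
|---|---|---|---|---|---|
| 19 | 0.8 | 0.3 | 67.0% | 52.7% | 71.0% |
| 19 | 0.8 | 0.5 | 67.0% | 67.0% | 79.1% |
| 19 | 0.8 | 0.7 | 67.0% | 87.2% | 91.9% |
| 25 | 0.8 | 0.3 | 79.1% | 64.9% | 82.7% |
| 25 | 0.8 | 0.5 | 79.1% | 79.1% | 89.2% |
| 25 | 0.8 | 0.7 | 79.1% | 94.7% | 97.2% |
| 19 | 0.5 | 0.3 | 32.3% | 24.5% | 34.9% |
| 19 | 0.5 | 0.5 | 32.3% | 32.3% | 40.9% |
| 19 | 0.5 | 0.7 | 32.3% | 49.1% | 55.5% |

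ANCOVA has the highest power in every row. The gain at 19 per arm and d = 0.8 runs from 4 to 25 points over week-12 ANOVA, and from 18 down to 5 points over change-score ANOVA, as ρ goes from 0.3 to 0.7.

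**Synergy as an interaction.** If hypothesis 2 were tested as a 2×2 interaction of 0.8 SD (variance 4σ²/n, 19 per arm), power would be 40.5% unadjusted, 51.0% with ANCOVA at ρ = 0.5 and 67.3% at ρ = 0.7. The direction is the same, from a lower starting point.

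**The case against.** A reader might infer that ANOVA is the declared default and that the collected baseline values go unused. The text supports neither. It lists ANOVA, ANCOVA and mixed models without naming a default, and the next sentence says relevant covariates will be included. An ANOVA of change would also use the baseline value, though less efficiently.

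It can also be said that these comparisons are described as exploratory, and that covariate lists for secondary outcomes are normally left to an analysis plan, which may exist. That holds for the detail of the list. It does not cover the rule the article does state: adjustment is conditional on an undefined need, and covariates are chosen by their relation to a different outcome. An analysis plan could follow that wording faithfully and still run an unadjusted FCAL comparison.

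Chance imbalance should not be counted as a second harm. Under randomisation a week-12 ANOVA is unbiased, and imbalance is already part of its larger standard error. The article also keeps the allocation code concealed until analysis is complete, which limits choices steered by the direction of effect. It does not supply the missing criterion.

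Finally, d = 0.8 was set for IBDQ-32, combination against double placebo. It cannot be carried over to FCAL, or to the combination against a single agent. This objection stands in full, so the power figures are illustrations.

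**Conclusion.** The point holds in a limited form. Baseline adjustment of the secondary between-group comparisons is optional, has no stated criterion, and is linked to a covariate rule built around quality of life. Unadjusted ANOVA is permitted where a method at least as precise, apart from one degree of freedom, is available from data already collected. The primary analysis is unaffected.

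It would go too far to conclude that the tests behind hypotheses 1 and 2 have lost a known amount of power. The article gives no FCAL effect, SD or correlation, does not say which ANOVA form would be used, and may yet lead to ANCOVA. The calculation also does not model the microbiome profile. The direction of the precision comparison is firm; its size depends on the assumed d and ρ. This is a free improvement to the plan and corrects no stated figure.

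**What to change.** Replace the conditional sentence with wording along these lines: each secondary outcome measured at baseline and week 12 will be compared between arms by ANCOVA of the week-12 value, with arm and that outcome's own baseline value as covariates, whether or not baseline imbalance is seen; mixed models for outcomes measured at three timepoints will also account for baseline.

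The mixed model may take baseline as a covariate or as a repeated response; either is sound if fixed in advance. The analysis scale for FCAL should likewise be chosen before unblinding and before any comparison by coded arm. A log scale is one option, but the article gives no distribution on which to settle it, and the stated assay range should be considered in that choice.

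The cost is one sentence of wording and one degree of freedom per ANCOVA model, with no extra participants, visits or measurements.
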